### Development of the intervention

All patient participants identified as potentially suitable for the study, will receive a letter of introduction, a study information sheet and provide written consent to participate in the research. Those who express an interest in the study will be invited to attend an open day where they can learn more about the research and decide whether or not they would like to take part. Preparatory patient learning journey (PLJ) workshops will be held for all patients participating in the training programme. These will be facilitated by members of the 'patient voice' group at the University of Leeds. These facilitators, who are patients and carers themselves, help to create a supportive learning environment where the patients feel comfortable about sharing their experiences and valued for their contribution. The approach focuses on three sessions:

a) The first session is on the 'patient journey' in which the patients are given the opportunity to think and talk about their own journey and share their experiences. This session particularly focuses on key contributory factors for safety such as hygiene, communication, medications and observations.

b) The second session allows patients to reflect on the content of the first session and discuss how things could have been done differently to improve their experiences with healthcare.

c) The third session builds on the first two sessions to allow patients to think about how their experiences and knowledge can help health professionals to learn and develop their own practice. In addition, it focuses on how these patients could be involved in teaching healthcare professionals. At the end of these sessions patients will have developed their experiences into a story of approximately 20 minutes in length that they will relay to trainees in the teaching session. The precise content of the talk is discussed within the patient voice group, but is largely decided upon by the patients themselves, e.g. the patients may choose to focus on one particular aspect of their experience, or supplement their talk with a PowerPoint presentation to clarify their message. To ensure patients are fully supported and feel confident they will be briefed before and after the teaching sessions. A third patient participant will also attend each teaching session to take observational notes and serve as a reserve, in case one of the patients is unable to attend.

### Intervention

The teaching session will use patient stories to focus both on the specific issues around the individual patient story as well as more generic issues around patient safety. Emphasis will be given to issues of analysis and causes of errors. The stories will include factual descriptions of what happened and reflections about their experience with medical error, what went wrong, why it took place, what the NHS response was, the impact of the error, the information they were given, what could be done better and why. The sessions will be interactive with questions and debate. Facilitation will be provided by a trained independent chairperson along with the patients. Participants will be asked to reflect on the patients' narrative, to identify key themes on patient safety emerging from the stories and to explore their own attitudes and beliefs towards patient safety. They will also be encouraged to share their own experiences of safety incidents, both as professionals and as patients or carers themselves.

### Measures

Measuring error is difficult [9]. It would be unrealistic to expect be able to detect or attribute changes in patient safety incident rates, for example through case note review, for junior doctor's practice as part of their multidisciplinary team. The primary aim of the patient-led teaching module is to facilitate awareness of patient safety issues, allow reflection on and facilitate changes to their attitudes to patient safety and above all, promote a safety culture among doctors at such an early stage of their training. It is hoped that this will translate into improved safety in practice.

Outcome measures for the study will combine quantitative and qualitative methods and include:

1. The Attitudes to Patient Safety Questionnaire (APSQ) [10], a reliable and validated 26-item questionnaire addressing patient safety attitudes. It was originally designed to target senior medical trainees which make it applicable to FY1 trainees at the start of their clinical practice.

2. Knowledge of patient safety will be measured using a reliable and validated 7 item measure specifically designed to target medical trainees [11]. Both measures will be administered to all trainees in both the intervention and control groups before and after the training session and 4-6 weeks later.

3. All trainees will be asked to complete a course evaluation at the end of the teaching session to assess overall effectiveness.

4. Twenty in depth interviews with a purposive sample of ten trainees from each group (control/intervention) will explore their views on the impact of medical error on patient outcome and the perceived usefulness and acceptability of the two training sessions. These will be conducted 4-6 weeks after the teaching session. Feedback from patients and experts suggests that patient stories provoke an emotional response in the learner. Trainees will be specifically asked about any psychological impact of the patient narratives on themselves with the intention of developing a measure to examine learning. Any differences in views on the perceived value and effectiveness of the two teaching sessions will be evaluated. The patients involved in the training will also be interviewed individually to explore their views on how effective the teaching programme was, how it had helped them understand the health system and reasons for medical errors. Transcripts will be content-analysed using thematic framework analysis. A constant comparative approach to the analysis of qualitative data will be used.

5. Observational notes will be taken by a third patient participant. The notes will focus on signs of audience engagement, levels of interest such as non verbal cues.

6. Trainees will be asked to identify up to 3 learning points that they identify at the end of the teaching session, that they intend to implement into practice. Trainees will be followed up at one month to see whether or not they have been successful in doing so.

### Analysis

We will undertake a regression based analysis adjusting for any clustering effects using the Huber-White approach as implemented in STATA. We will adjust for baseline test scores.

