#### b) Trainee doctors

In West Yorkshire there are currently 290 FY1 trainees enrolled. Eleven teaching sessions are conducted with approximately 26 trainees attending each session (intervention or control). In NEYNL, approximately 150 trainees will be enrolled as FY1. Ten teaching sessions on patient safety are conducted; therefore approximately 15 trainees attend each session (Figure 1). Each session will be equally divided, with approximately 7-8 trainees receiving the control and 7-8 receiving the intervention, as illustrated with Scarborough in Figure 1.

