### Sample Size calculation

In NEYNL, there are 150 trainees that will be allocated into 20 groups of 7-8 trainees. Assuming an intracluster correlation coefficient of 0.05 this gives a design effect of 1.3. The effective sample size, therefore, is 150/1.3, which is 115. This gives us approximately 80% power to demonstrate an effect size of 0.53.

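### Huber-White errors on 20 teaching groups, paired within 10 sessions, can misstate the error rate in either direction; the NEYNL analysis should account for session and use a small-sample method

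*Protocol article*

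**What the plan says.** The Analysis section of the protocol article is two sentences long. The first names the method: "We will undertake a regression based analysis adjusting for any clustering effects using the Huber-White approach as implemented in STATA". The second adds: "We will adjust for baseline test scores". Neither names the cluster unit, a reference distribution or a term for session.

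The Sample Size calculation places the powered comparison in NEYNL: "In NEYNL, there are 150 trainees that will be allocated into 20 groups of 7-8 trainees". It puts the clustering on those groups: "Assuming an intracluster correlation coefficient of 0.05 this gives a design effect of 1.3". The sections on setting and on trainee doctors describe ten NEYNL sessions in which both arms run side by side, with trainees randomised on the day: "Each session will be equally divided, with approximately 7-8 trainees receiving the control and 7-8 receiving the intervention". So the 20 groups form 10 pairs. The West Yorkshire phase comes first, serves to refine the methods, and is not counted in the power calculation.

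**The concern.** The cluster-robust (sandwich) variance is justified for many clusters. With 10 groups per arm and a treatment that varies between groups, group residuals are taken around an estimated arm mean, and the variance comes out too small unless corrected.

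The design also has a feature that pulls the other way. Anything that the two groups in a session share (hospital, day, intake) cancels from the treatment contrast. A group-clustered variance without session terms still counts it, and is then too large.

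At stake is whether the p-value and confidence interval for the primary outcome, the APSQ score, mean what they say.

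**Working it through.** **Inputs.** From the article: 150 trainees, 20 groups, mean size m = 7.5, 10 groups per arm, 10 sessions, ICC 0.05, baseline adjustment. Assumed, because not stated: two-sided 5% level, baseline correlation of about 0.5 in the simulations, and Stata's linear-regression default taken as the factor G/(G-1) x (N-1)/(N-k) with t on G-1 df.

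**Step 1: the plan's own figure.** Design effect = 1 + 6.5 x 0.05 = 1.325 (stated 1.3). 150/1.3 = 115.4, or 57.7 per arm. Power for 0.53 is 81.2% (normal) or 80.6% (noncentral t). The stated 80% is reproduced, as an individual-level calculation on the effective sample size.

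**Step 2: all clustering at group level.** The plain sandwich variance is about 9/10 of the truth. Stata's factor with three parameters is 20/19 x 149/147 = 1.067, so the ratio becomes 0.9 x 1.067 = 0.960 and the standard error is about 2% too small. Treating the statistic as t on 18 df:
- Factor and t(19): P(|t18| > 2.093 x √0.960) = 5.5%.
- Factor and normal reference: P(|t18| > 1.96 x √0.960) = 7.1%.
- Plain sandwich and normal reference: P(|t18| > 1.96 x √0.9) = 7.9%.

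Simulations with the baseline covariate give 5.3-5.8% (6.0% when group sizes run from 4 to 11), 6.9-7.3% and 7.8-8.3% respectively.

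**Step 3: part of the clustering shared within session.** Take total variance 1. A group mean has variance 0.05 + 0.95/7.5 = 0.1767. The group-clustered method estimates the contrast variance as (2/10) x 0.1767 x 0.960. If a share s of the ICC lies at session level, the true value is (2/10) x (0.1767 - 0.05s).

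| s | Ratio, estimated to true variance | Type I error, factor and t(19), approximate | Simulated |
|---|---|---|---|
| 0 | 0.96 | 5.5% | 5.3-5.8% |
| 0.5 | 0.960 x 0.1767/0.1517 = 1.12 | 4.0% | 3.7-4.4% |
| 1 | 0.960 x 0.1767/0.1267 = 1.34 | 2.6% | 2.1-2.9% |

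The variance ratio passes 1 at s = 0.04 x 0.1767/0.05 = 0.14. About one seventh of the clustering being shared is therefore enough to turn a slightly small standard error into a slightly large one.

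**Step 4: a method that respects the pairing.** A t-test on the 10 baseline-adjusted within-session differences (9 df) has simulated type I error of 4.9-5.4% whether none, half or all of the clustering is shared. By contrast, a bias-reduced sandwich (CR2) with 18 df and an unpaired t-test on the group means return to 5.1% and 5.2% only when all clustering is at group level. The unpaired t-test is also off once sessions share variation.

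**The case against.** The strongest reply has four parts.

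- **The article does not fix an uncorrected method.** It says Huber-White as Stata implements it, which for linear regression plausibly includes a finite-sample factor and a t reference. The excess is then well under one percentage point in most runs and at most about one. This stands. A reader might infer that 20 clusters are simply too few for the method or that the inflation is gross; the figures do not support that. The 7-8% values need a normal reference, which the article never states.
- **Parallel sessions can remove the inflation altogether.** This also stands, and it rules out an unconditional claim that type I error exceeds 5%. It does not rescue the method: a test at 2-4% when 5% is intended is also miscalibrated.
- **Other cluster units behave differently.** Clustering on the 10 sessions gives 4.7% with t(9), and on the five sites 5.3% with t(4), in simulations with group-level clustering and Stata's factor. A reader might infer that clustering on hospitals must inflate type I error; with a t reference it does not. With the plain sandwich and a normal reference the figures are 9.6% and 16.3%. Pooling West Yorkshire would give 31 clusters and 6.2% with t(30), so a larger cluster count does not settle the matter.
- **A journal article leaves detail to a fuller document.** Fair for the bare omission of cluster unit and degrees of freedom. But a method is named here, its performance on this design can be computed, and a better-calibrated one is available.

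**Conclusion.** The point holds as a modest calibration problem of uncertain sign. For the NEYNL comparison, group-clustered Huber-White errors without session terms give type I error of about 5.3-6% (t reference) or 7-8% (normal reference) if all clustering is specific to the teaching group. With the t reference they give about 3.7-4.4% if half is shared within session, and about 2-3% if all is.

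The result rests on the article's ICC of 0.05 and 20 groups of 7-8, on group as the cluster unit (which the sample size section implies but the Analysis section does not state), and on the assumed Stata default. The article does not say how the clustering divides between session and group, so the direction cannot be settled from it. The change is worth making because it removes that dependence at little cost, not because the named method fails badly.

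**What to change.** In the NEYNL analysis of the primary outcome, account for session and name a small-sample method. Any of these would do:
- a t-test on the 10 baseline-adjusted within-session differences, 9 df;
- a mixed model with session and group-within-session effects and Kenward-Roger degrees of freedom;
- regression with session terms, clustered on teaching group, with CR2 variance and Satterthwaite degrees of freedom.

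**Cost.** Analysis wording only; no change to recruitment or conduct. Degrees of freedom fall. Take the first option and the variances above. Its 95% half-width with no shared clustering is 2.262 x √(0.2 x 0.1767) = 0.425 SD, against 2.093 x √(0.2 x 0.1767 x 0.960) = 0.385 SD for the present method. With half shared it is 2.262 x √(0.2 x 0.1517) = 0.394, and with all shared 2.262 x √(0.2 x 0.1267) = 0.360. So intervals are about 10% wider at worst and narrower at best.

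Power for 0.53 should be restated with the chosen method. With group-only clustering it is about 75-76% on 18 df. On 9 df it is about 71% (noncentrality 0.53/√(0.2 x 0.1767) = 2.82). Both figures ignore any gain from baseline adjustment, and power rises if sessions share variation.

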## Discussion

The strength of this research is our commitment to patient involvement. The patients in our study will not only deliver the intervention, but will be involved in defining the aims and objectives of the teaching sessions, provide feedback on documents, e.g. our interview guide for trainee doctors; and will take part in focus groups after the teaching sessions to refine the intervention. This will require considerable commitment from the patient and in recognition of their contribution they will be provided with financial reimbursement for their attendance on the teaching and training days, in addition to travel expenses.

This research also poses a number of challenges. Firstly, patient safety teaching is already established in both West Yorkshire and NEYNL. The research team must therefore negotiate the integration of the study into the existing teaching curriculum. This requires careful consideration of pre-existing learning outcomes to ensure that the teaching fulfils the Foundation School's obligation to provide comprehensive safety training. The research team must also work closely with Foundation Year 1 co-ordinators and facilitators to ensure successful implementation of the study. Secondly, there is little evidence of optimal objective outcome measures for educational interventions, particularly in the medium or long term. There is also a lack of consensus as to whether attitudes can be changed and whether these changes will necessarily translate into professional behaviour. To address this challenge we intend to use a variety of measures, i.e. questionnaires, interviews, focus groups and self reported learning to provide a richness of data.
